#### Translational research

Archival fixed paraffin embedded (FFPE) tumour samples will be collected at baseline on all patients. New tissue biopsy will be collected at week 6 (week 1 of brachytherapy). Sections will be cut by histology for the following analyses: H&E stain for pathology reporting, RNA extraction for transcriptomics, Immunohistochemistry (IHC) for IAP and hypoxia status and DNA extraction for investigating the mutational landscape. Cores may also be taken for construction of Tissue Microarrays (TMAs).

Translational blood samples will be collected at every visit, except the final follow-up visit (week 18). One sample will be to study “on-target” effects of tolinapant by measuring cIAP levels in PBMCs. The rest will enable biomarker discovery. This data will enable powering of a future phase II study for biomarker validation, thus enabling both biomarker and clinical development to occur in parallel.

Translational urine samples will be collected at baseline, week 1,3 and 5 (on during RT), week 6 (during brachytherapy) and at both follow up visits. Urinary cell-free DNA (ucfDNA) will be extracted from these samples in order to explore the urine biomarkers associated with treatment response and toxicity.

Collection of translational samples will be part of the main study consent form. Any samples remaining once trial analyses are complete will be stored appropriately for future use, if patient consent allows.

#### Contraception

Women of child-bearing potential must agree to use one of the following methods of contraception effective from the first administration of all study drugs, throughout the trial and for six months afterwards: sexual abstinence, bilateral tubal occlusion, vasectomized partner, a barrier method such as male or female condom (with or without spermicide), cap or diaphragm.

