**Exclusion criteria**	
1.	Previous pelvic radiotherapy
2.	Liver cirrhosis, or chronic liver disease Child-Pugh Class B or C
3.	Women who are pregnant or breast feeding (WOCBP must have a negative serum pregnancy test at screening)
4.	Patients of child-bearing potential who are not able to use a method of contraception as detailed in Sect. 4.6
5.	Any investigational medicinal product within 30 days prior to consent
6.	Major surgery within 30 days prior to enrolment
7.	Hypersensitivity to tolinapant, excipients of the drug product, or other components of the study treatment regimen
8.	Patients with known HIV infection
9.	Patients with known active hepatitis B virus (HBV; chronic or acute; defined as having a positive hepatitis B surface antigen [HBsAg] test) or hepatitis C. Patients with past HBV infection or resolved HBV infection (defined as the presence of hepatitis B core antibody and the absence of HBsAg) are eligible. Patients positive for hepatitis C virus (HCV) antibody are eligible only if polymerase chain reaction is negative for HCV RNA
10.	Coronary artery bypass graft, angioplasty, vascular stent, myocardial infarction, unstable arrhythmias, unstable angina, left bundle branch block, third degree heart block, pacemakers or congestive cardiac failure (New York Heart Association ≥ grade 2) within 6 months prior to enrolment
11.	Any patient who has received a live vaccine within 4 weeks of initiation of their treatment (COVID-19 vaccination is allowed).
12.	Conditions requiring systemic treatment with either corticosteroids (≥ 20 mg daily prednisolone or equivalent) or other immunosuppressive medications within 14 days of study drug administration

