#### Screening

Following consent, patients undergo screening assessments that should be completed within 2 weeks of treatment, with the exclusion of the diagnostic/baseline scans, which can be done within 8 weeks prior to treatment. Assessments include physical examination, ECOG performance status, ECG, echocardiogram, serum biochemistry (including renal, liver, bone and thyroid profiles, plus random cortisol and glucose levels), haematology and serology (HBV and HCV). Concomitant medication and medical history will be recorded. In addition, women of childbearing potential (WOCBP) will undertake a pregnancy test.

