#### Treatment and follow-up visits

Treatment will consist of standard of care CRT with 45 Gy external beam radiotherapy administered in 25 daily fractions over 5 weeks with once weekly cisplatin 40 mg/m2. RT visit assessments include ECOG performance status, routine bloods, pregnancy tests for WOCBP (weeks 3 & 5) and adverse event assessment (weeks 1, 3 & 5). Six PK samples will be taken across day 4 and day 5 of week 1.

Tolinapant will be administered in fixed dose capsules of 30 mg or 90 mg taken orally daily for seven consecutive days as an outpatient (followed by seven consecutive days off) prior to radiotherapy on alternate weeks (weeks 1, 3, 5) during chemoradiation. As tolinapant will be administered as an outpatient, and in order to assess IMP administration adherence, patient diaries will be reviewed and capsule returns monitored. Tolinapant can be taken with or without food, with the exception of PK days. On days with PK sampling, patients should refrain from eating (including soup) or drinking milk or juice for at least 2 h prior to ingesting study drug(s) and 2 h after ingesting study drug (4 h fasting window).

This is followed by standard of care brachytherapy. Assessments during brachytherapy visits will include physical exams, ECOG performance status, routine bloods (week 6 only) and adverse event assment (week 7 only).

Patients will then attend a follow-up visit at weeks 12 and 18, involving physical exams (including vaginal adhesions at week 18), ECOG performance status, adverse event assessment, MRI (week 18 only) and Disease Assessment Questions (week 18 only).

The Schedule of Events (Table 2) details the trial treatment schedule.

**Table 2 Tab2:** Schedule of observations and procedures

	Screening Phase	Treatment Phase							Follow up Phase	
		External Beam RT Treatment Week 1	External Beam RT Treatment Week 2	External Beam RT Treatment Week 3	External Beam RT Treatment Week 4	External Beam RT Treatment Week 5	Brachytherapy Week 1	Brachytherapy Week 2	Follow up visit 1	Follow up visit 2
Trial Week^1^	-2-0 weeks	1	2	3	4	5	6	7	12 (± 1 week)	18 (± 1 week)
Informed consent^2^	x									
Inclusion / exclusion criteria	x									
Medical history	x									
Physical exam	x						x	x	x	X^3^
ECOG performance status	x	x	x	x	x	x	x	x	x	x
Electrocardiogram	x									
Echocardigram	x									
Serum biochemistry^4^	x	x	x	x	x	x	x			
Haematology^5^	x	x	x	x	x	x	x			
Serology – HBV and HCV	x									
Pregnancy test for WOCBP^6^	x			x		x				

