Translational tissue samples^7^	x						x			
Translational blood samples	x	x	x	x	x	x	x	x	x	
Translational urine samples	x	x		x		x	x		x	x
Diagnostic imaging assessment (MRI)	X^8^					x				X
CT scan to assess for metastases^9^	x									
Disease Assessment Questions^10^	x					x				x
Adverse event assessment	x	x		x		x		x	x	x
Concomitant medication record	x								x	x
Tolinapant^11^		x		x		x				
PK sampling^12^		xxxxxx								
External beam radiotherapy (standard 5 week course)^13^		x	x	x	x	x				
Cisplatin (40 mg/m^2^)		x	x	x	x	x				
Brachytherapy^14^							x	x		

^1^Treatment weeks of CRT and tolinapant should always be scheduled to start on a Monday, cisplatin can be given on any day throughout the week

^2^Consent may be taken up to 14 days prior to Treatment day 1, week 1 and must be completed before any screening procedures take place

^3^Vaginal adhesions should be assessed as part of the physical exam at the follow up 2 visit to inform the disease assessment

^4^Serum biochemistry including renal (urea, sodium, potassium, creatinine), liver (AST and ALT, ALP and bilirubin), bone (including serum albumin and calcium), thyroid profiles (including T4, T3, TSH) and lipids, lipase and amylase. Bloods required on the day of treatment can be taken up to one working day in advance

^5^ Full blood count (FBC) to include haemoglobin, white blood cell count, absolute neutrophil, lymphocytes and platelets counts. Bloods required on the day of treatment can be taken up to one working day in advance

^6^Must be serum test at screening. Urine/serum test at week 3 and week 5

^7^ Archival FFPE block to have been collected within 3 months prior to day 1 and should be sent as soon as possible after consent. New tissue biopsy to be collected at week 1 Brachytherapy

^8^Screening scan not required if done within 8 weeks prior to day 1

^9^Baseline imaging assessing for metastases can be done via CT alone or combined PET-CT, and does not need to be repeated if done within 8 weeks prior to day 1

^10^Assessment of fecal urgency (RT-ARD Score) at screening, Radiotherapy week 5 and follow up 2. Assessment of vaginal dilator use at follow up 2 only

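### Contraception starts only at the first dose and no pregnancy test is repeated before it, leaving up to 14 days after the screening test uncovered before first tolinapant exposure

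*Protocol article*

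**What the plan says.** All references are to the protocol article.

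- **Start of contraception** (Contraception): required of women of childbearing potential "effective from the first administration of all study drugs, throughout the trial and for six months afterwards". No earlier start is given anywhere. Exclusion 4 in Table 1 only refers to the contraception rule, in Sect. 4.6 of the full protocol.
- **Test for eligibility** (Table 1, exclusion 3): "WOCBP must have a negative serum pregnancy test at screening".
- **Timing of screening** (Screening): "patients undergo screening assessments that should be completed within 2 weeks of treatment". Table 2, footnote 2 adds "Consent may be taken up to 14 days prior to Treatment day 1, week 1", and consent must come before any screening procedure.
- **Tests on treatment** (Treatment and follow-up visits): "pregnancy tests for WOCBP (weeks 3 & 5) and adverse event assessment (weeks 1, 3 & 5". Table 2, footnote 6 agrees: "Must be serum test at screening. Urine/serum test at week 3 and week 5". The pregnancy row of Table 2 has no mark at week 1.
- **Tolinapant**: seven daily doses in each of weeks 1, 3 and 5.

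**The concern.** Exclusions 3 and 4 are there to keep tolinapant from pregnant women. Between the screening test and the first dose, which can be 14 days, the plan asks for neither contraception nor a second test. Two kinds of pregnancy can pass through: one conceived after the screening test, and one conceived shortly before it and not yet detectable.

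The schedule is also uneven. Weeks 3 and 5 are about 14 days apart, contraception is compulsory throughout, and a retest is still required. Screening and day 1 can be equally far apart, contraception is not yet compulsory, and there is no retest. That less protected interval is the one in which a positive result could still prevent any tolinapant exposure.

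What is at stake is fetal exposure to an investigational drug. The radiotherapy and cisplatin are standard of care, so only the tolinapant exposure is added by the trial. The dose-finding model and the operating characteristics of the design are not affected.

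**Working it through.** The article states no figure to reproduce. The check has two parts: whether the passages agree, and what the calendar implies.

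**Agreement.** The visit text, the Table 2 row and footnote 6 give the same test schedule. One sentence of the visit text places adverse event assessment in weeks 1, 3 and 5 but pregnancy tests in weeks 3 and 5 only. The empty week 1 cell is therefore the stated rule and not a lost table entry. Nothing contradicts anything else; the gap lies in the rule.

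**Inputs.**
- Day 1 is a Monday (Table 2, footnote 1: "Treatment weeks of CRT and tolinapant should always be scheduled to start on a Monday").
- Earliest screening test: day 1 minus 14.
- Week 3 test: Table 2 fixes the week but not the day, so Monday (day 15) to Friday (day 19).
- Tolinapant on days 1–7, 15–21 and 29–35: 3 × 7 = 21 doses.
- Radiotherapy: 45 Gy / 25 = 1.8 Gy per fraction, five per week.
- Cisplatin once weekly, on any day of the week.

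**Results, with screening at its earliest.**

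| Quantity | Week 3 test on Monday (day 15) | Week 3 test on Friday (day 19) |
|---|---|---|
| Screening test to week 3 test | 14 + 14 = 28 days | 14 + 18 = 32 days |
| Days without required contraception | 14 | 14 |
| Tolinapant doses before the test | 7 of 21 | 7 + 4 = 11 of 21 |
| Fractions before the test (standard of care) | 10 × 1.8 = 18 Gy | 14 × 1.8 = 25.2 Gy |
| Cisplatin doses by then (standard of care) | 2 of 5 | up to 3 of 5 |

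With later screening, the uncovered period shrinks towards 0 days and the interval between tests shortens with it. The number of tolinapant doses before the week 3 test does not change.

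**What each remedy covers.** Contraception from consent covers all 14 days after the screening test, because consent precedes that test. It cannot help with a conception before consent.

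For a repeat test on day 1, suppose a test turns positive L days after conception, with L between 7 and 14. This range is an assumption; the article gives none. With screening 14 days earlier, the day 1 test detects conceptions from only the first 14 − L days of the window, that is 14 − 7 = 7 days down to 14 − 14 = 0 days. It also detects those conceived in the L days before screening, which the screening test missed and which are at least 14 days old by day 1. The two remedies therefore cover different cases, and contraception from consent is the stronger for the window itself.

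**The case against.** The strongest reply is that nothing here is an error. The schedule can be read as one test for each tolinapant course (screening, week 3, week 5), with the stricter serum test first, so a fourth test is a matter of preference. Pregnancy is an exclusion in its own right, as is inability to use contraception. A method must be in place by the first dose, and two of the listed methods (tubal occlusion and a vasectomised partner) would normally be working already during screening. The figures are maxima: they need screening on the earliest permitted day, and the upper ones also need a week 3 test left until Friday. The chance of conception is likely low, and radiotherapy and cisplatin would be given in any case. Sect. 4.6 of the full protocol might set an earlier start for contraception. Finally, a day 1 test misses much of the window.

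Most of this limits the size of the point, and it is accepted in that sense. It does not close the gap. A method that must work at the first dose says nothing about the preceding days, and the exclusions act through a test that may be 14 days old. One test per course does not give equal protection, because only the first interval lacks compulsory contraception. The unseen Sect. 4.6 matters more for the contraception start than for testing: a further pre-dose test there would contradict the article's own text, table and footnote. The weakness of a day 1 test is a reason to put contraception first, not to leave both as they are.

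**Conclusion.** The concern holds. As written, the plan leaves 0 to 14 days after the screening test with no contraception required and no retest before first exposure. In the worst case the screening and week 3 tests are 28 to 32 days apart, with 7 to 11 of 21 tolinapant doses taken in between; at least one full course always precedes the second test.

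It applies only to women of childbearing potential, and only to a conception after the screening test or too early for that test. The article gives neither their share nor a conception rate, so no expected number of cases can be calculated. This is a participant-safety gap of likely low probability that is cheap to close, and it has no consequence for dose finding. Confidence is medium because the full protocol's contraception section is not shown.

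**What to change.** 1. **Main change.** In the Contraception section, and in Sect. 4.6 of the full protocol if it reads the same, make the duty start at informed consent instead of at the first administration of study drugs, and leave its end date as it is. Uncovered days after the screening test fall from up to 14 to 0. Abstinence and barrier methods are on the permitted list and can begin at once, so this need not delay treatment.

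2. **In addition.** Mark week 1 in the pregnancy row of Table 2 and amend footnote 6 and the visit text to match: urine or serum, with the result available before the first tolinapant dose. State that this test may miss a very recent conception; its main value is for a pregnancy too early for the screening test. With the test on day 1, the longest interval between tests falls from 28–32 days to 14 days, or 18 if the week 3 test is done on the Friday (day 19 − day 1).

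**Cost.** One clause, one table mark and its matching text, one assay per woman of childbearing potential, and a contraception duty up to 14 days longer. No extra visit is needed: footnote 4 to Table 2 says "Bloods required on the day of treatment can be taken up to one working day in advance", so a serum test can go with the week 1 bloods. Urine is also collected in week 1, but for translational work and without a stated time relative to dosing. If urine is used, the protocol should say that it is taken and read before the first dose.

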### Data collection and management

#### Plans for assessment and collection of outcomes

Data will be entered into the electronic case report forms (eCRFs) within Medidata Rave by the relevant trained site research team personnel. The data entered will be regularly checked by SCTU for missing or anomalous values and data queries will be automatically or manually generated withing the eCRF.

The Patient Information Sheet (PIS) and Informed Consent Form (ICF) will outline the participant data to be collected and how it will be managed or might be shared, including handling of all Patient Identifiable Data (PID) and sensitive PID adhering to relevant data protection law.

#### Data management

A data management plan has been developed for CRAIN which provides a complete overview of the organisation of data management products and procedures. Participant data will be entered remotely at site and retained in accordance with the current Data Protection Regulations. The Principal Investigator (PI) at each site is responsible for ensuring the accuracy, completeness, and timeliness of the data entered. Only the investigator and personnel authorised by them should enter or change data in the eCRFs.

The participant data is pseudo anonymised by assigning each participant a participant identifier code which is used to identify the participant during the trial. The site retains a participant identification code list, which is only available to site staff.

Data queries will either be automatically generated within the eCRF, or manually raised by the SCTU, if required. All alterations made to the eCRF will be visible via an audit trail.

At the end of the trial, when the last patient has had their last trial visit and after all queries have been resolved and the database frozen, the PI will confirm the data integrity by electronically signing all the eCRFs. The eCRFs will be archived according to SCTU policy and a PDF copy including all clinical and Meta data returned to the Investigator for each participant.

### Oversight and monitoring

The Trial Management Group (TMG) is responsible for overseeing progress of the trial, including both the clinical and practical aspects, and is comprised of clinicians, statisticians and Patient and Public Involvement (PPI) contributors and other SCTU staff. The Chair of the TMG is the Chief Investigator (CI) of the trial. The Trial Steering Committee (TSC) acts as the independent oversight body on behalf of the Sponsor and Funder, and has a majority independent of the trial. The Safety Review Committee (SRC) contains an independent clinician and statistician, alongside the CI and PIs and SCTU staff, and will review and assess the safety and toxicity of all patients at each dose, decide the recommended dose cohort for future patients, decide the maximum number of patients to recruit on that dose, and will determine whether the trial should continue or stop (due to patient safety and/or feasibility issues or the reaching of the MTD). Charters for these groups can be obtained via [contact].

The trial may be subject to inspection and audit by University Hospital Southampton NHS Foundation Trust (as Sponsor), SCTU (as the Sponsor’s delegate) and other regulatory bodies to ensure adherence to the principles of Good Clinical Practice (GCP), Research Governance Framework for Health and Social Care, applicable contracts/agreements and national regulations.

A risk assessment for CRAIN has been carried out to identify potential risks and to document any required mitigations that may be required. Following the risk assessment, a trial monitoring plan was developed to detail the expectation for both central and on site monitoring. Data required to inform decision making and to determine the safety of the experimental treatment will undergo full central monitoring. All sites are subject to on-site monitoring, where SCTU will be given direct access to source documentation for verification of data entered onto the eCRF. Monitoring procedures are fully described in the trial’s monitoring plan. Participants’ medical records and other relevant data may also be reviewed during audit of the trial. Details will remain confidential and participants’ names will not be recorded outside the trial site without informed consent.

### Patient and public involvement

There are currently three active PPI members contributing to CRAIN who all have direct experience of cervical cancer, either as a patient or carer. While the trial is active the SRC, TMG and trial steering committee groups will all have PPI representation to assist in the ongoing oversight of the trial. In addition, there has been PPI contribution to the development of the protocol, PIS and ICF. The PPI members have also played a significant role in raising awareness for the trial through various media coverage.

### Statistical analysis

A detailed statistical analysis plan will be developed prior to database lock, and all data and appropriate documentation will be stored for a minimum of 25 years after the completion of the trial. All eligible participants enrolled in the study will be accounted for in the safety analysis. The primary analysis will be based on the principal stratum strategy of the Estimand framework [8] where patients who do not receive any exposure to tolinapant will not be included in the analysis and will be replaced.

DLTs are defined in the *Dose Limiting Toxicology* section.

#### Dose escalation and determination of MTD

The trial will be a single arm, open-label, multi-centre trial that will use the two-stage time-to event continual reassessment method (TiTE-CRM) to find the optimal dose of tolinapant in combination with CRT. This method assigns weights to the amount of time a patient spends in the study without experiencing a DLT and allows for dose decisions to be made without having to wait for full information from each participant enrolled. This allows for a potentially shorter trial duration without sacrificing valuable data. Simulations (see additional file 1) were run to see how this design perfomed under a range of scenarios for the true toxicity levels of the doses and to compare with a standard 3 + 3 cohort design. The optimal dose will be defined as the dose where the proportion of patients experiencing a DLT is closest to the target toxicity rate. DLTs for existing treatment is thought to be in the range 5 to 15%. The target toxicity rate was therefore chosen as 25% as an acceptable rate above this.

Dose levels for tolinapant which will be assessed in the TiTE-CRM are: Level 1: 60 mg; Level 2: 90 mg (starting level); Level 3: 120 mg; Level 4: 150 mg; Level 5: 180 mg. No dose skipping is allowed (i.e., it is only possible to escalate to an adjacent dose). These doses were thought to cover a range of outcomes from a low number of DLTs to those plausibly at, or potentially beyond, the target toxicity rate. The two-stage design allows more control of the dose escalations in the early stages of the study when no DLTs have occurred. The TiTE-CRM model together with emerging safety data will guide escalation decisions but all decisions will be made by the SRC.A maximum of 42 patients will be recruited and treated according to the dose defined by the TiTE-CRM. The first patient recruited will be assigned 90 mg as this will allow for a dose reduction to 60 mg for future patients if the first patients experience excess toxicity. The TiTE-CRM will identify the MTD based on the assessment of dose limiting toxicities (DLTs), this will be used to aid the SRC when determining the recommended phase II dose.

The TiTE-CRM design utilises a one parameter logistic model and linear weights. Meaning that information accrued through the DLT assessment period (12 weeks from the start of treatment) is given weight equal to the proportion of the assessment period that has passed. Any patient experiencing a DLT will be included in the analysis as a full patient equivalent, regardless of the timing of the event. Any patient who discontinues treatment early, for any reason not attributable to a DLT, will be included in the analysis as a patient without a DLT. The Safety Review Committee (SRC) will decide whether an extra patient should be recruited to the current dose based on the amount of treatment they had received.

The treatment schedule is planned to last 7 weeks, with an additional 5 weeks follow up for DLTs. Linear weighting will be used in the TiTE-CRM. For example:

At trial week 12 (i.e. completion of treatment and 5 weeks of follow-up): in the absence of a DLT this would account for a full patient tolerable outcome.At trial week 6: in the absence of a DLT this would account for 0.5 equivalent of a tolerable outcome.

The trial will stop for success if 15 consecutive patients are treated at the current recommendation for the MTD, whilst also ensuring a total of at least 18 patients have been treated at the recommended phase II dose. The trial will stop for safety if there is sufficient evidence to suggest that dose level 1 (60 mg) is too toxic i.e. a posterior probability of DLT of 35% or higher is found reflecting a 10% increase over the expected toxicity rate based on published experience [3]. For more information on the TiTE-CRM design and the stopping rules for the study please see additional file 1.A SRC will be responsible for confirming trial dose escalations within the trial, informed by the dose-toxicity model and safety data. The SRC will decide if patients should be replaced based on the amount of treatment received.

If a fifteenth consecutive participant is treated at a given dose and 18 patients overall have been treated at this dose, no more participants will be recruited. All participants should then be followed up until a DLT or 12 weeks, the model and the MTDare then updated with this information, and this is used to inform the SRC’s decision on the final recommended phase II dose.

At the end of this phase, dose finding data will be summarised descriptively, including baseline characteristics for participants. Dose delivery and toxicities will be reported. Toxicities will be reported by cohort, including type, number, range and worst grade. Complete and partial response rates at 3 months after treatment, measured using Recist v1.1 criteria, will also be summarised descriptively along with relative dose intensity.

The parameters of the dose-toxicity model will be described alongside Bayesian posterior point estimates of the risk of toxicity at each dose and corresponding 95% credible intervals.

All analysis will be done in R, Stata v16 or higher, or SAS v9.4.

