#### Dose limiting toxicology

The DLT assessment period is 12 weeks from the start of treatment.

Any of the following events occurring after the first dose of tolinapant will constitute a DLT if, in the opinion of the investigator, the event is defined as definitely or probably related to tolinapant:

Grade 4 neutropenia ≥ 7 days duration.Grade 3 or 4 febrile neutropenia (neutrophils < 1000/mm3 with a single temperature of > 38.3 °C or a sustained temperature of ≥ 38 °C for more than one hour AND/OR life-threatening consequences with urgent intervention indicated).Grade 3 or 4 neutropenia associated with a separate event of bacteriologically proven sepsis happening at the same time.Grade 3 or 4 thrombocytopenia.Death.

Any other grade 3 or 4 adverse event will constitute a DLT if, in the opinion of the investigator, the event is defined as definitely or probably related to tolinapant.

In all cases of a suspected DLT, clinical judgement will be the final arbiter as to whether the event should be categorised as such.

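### The ± 1 week tolerance lets the week-12 follow-up visit fall before the 84-day DLT period ends, yet the TiTE-CRM weight still rises to 1.0 with no scheduled check of the remaining days (minor)

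*Protocol article*

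**What the plan says.** The section on dose limiting toxicology sets the endpoint window: "The DLT assessment period is 12 weeks from the start of treatment". The section on dose escalation and determination of MTD builds the weights on it. The window is split into treatment and follow-up: "The treatment schedule is planned to last 7 weeks, with an additional 5 weeks follow up for DLTs". Information accrued during the window "is given weight equal to the proportion of the assessment period that has passed". Two worked examples follow: "At trial week 6: in the absence of a DLT this would account for 0.5 equivalent of a tolerable outcome", and at trial week 12, described as the end of treatment plus five weeks of follow-up, "in the absence of a DLT this would account for a full patient tolerable outcome". Once the stopping rule for success is met, "All participants should then be followed up until a DLT or 12 weeks"; the model and the MTD are then updated to inform the recommended phase II dose.

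On visits, the section on treatment and follow-up states: "Patients will then attend a follow-up visit at weeks 12 and 18". Table 2 gives each of these a tolerance of ± 1 week. Its adverse event row is marked at screening, weeks 1, 3, 5 and 7, and the two follow-up visits, so follow-up visit 1 is the only scheduled assessment between week 7 and week 18.

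The section on adverse event reporting ends the reporting of AEs and SAEs 30 days after the last tolinapant dose.

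**The concern.** The DLT is the primary endpoint and the only outcome that enters the dose-toxicity model. The weight rule counts elapsed days. The schedule lets the one assessment near the end of the window be held before the window closes. A patient seen early and free of DLT keeps gaining weight until day 84, although nobody is scheduled to look at the days in between. The next scheduled assessment is week 18 ± 1 week, and the final update is triggered at a DLT or 12 weeks, so it need not wait for that visit.

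At stake is a small, one-directional loss of DLTs: events in the last days of the window can be missed, but none are added. How much is lost depends on where in the tolerance each visit happens to fall.

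**Working it through.** **Inputs.** DLT period 12 weeks = 84 days (dose limiting toxicology). Linear weight, follow-up to a DLT or 12 weeks, and at least 18 patients at the recommended dose (dose escalation and determination of MTD). Target rate 25% (same section). Follow-up visits at week 12 ± 1 and week 18 ± 1, with the first treatment week labelled trial week 1 (Table 2). Treatment weeks start on a Monday (Table 2, footnote 1).

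**1. The plan's own weights.** Weight = elapsed days / 84. Week 6: 42/84 = 0.5. Week 12: 84/84 = 1.0. Both reproduce, provided that week k means k completed weeks. The start of calendar week 6 (35 completed days) would give 35/84 = 0.417.

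**2. Earliest permitted visit.**
- Completed weeks (the reading that fits the stated weights): 84 − 7 = day 77, a gap of 7 days.
- Calendar weeks (the labelling of Table 2): trial week k covers days 7(k−1)+1 to 7k. Week 11 is days 71-77, week 12 is days 78-84, week 13 is days 85-91. The earliest visit is day 71, a gap of 84 − 71 = 13 days. Even a visit on the first day of week 12 leaves 84 − 78 = 6 days.

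**3. Weight not backed by an assessment.**
- Day 71: weight 71/84 = 0.845, so 0.155 is added by day 84.
- Day 77: weight 77/84 = 0.917, so 0.083 is added.
- If all 18 patients at the recommended dose were seen that early, the total would be at most 18 × 0.155 = 2.8 or 18 × 0.083 = 1.5 patient-equivalents.

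**4. Apparent DLT rate when the true rate is 25%.** Assume that nothing after the visit on day d is captured.
- Uniform risk: 25% × d/84.
- 70% of risk in weeks 1-6 (an assumption, for range): 25% × (0.7 + 0.3 × (d − 42)/42).

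| Visit | Uniform risk | 70% early |
|---|---|---|
| Every patient on day 71 | 21.1% | 22.7% |
| Every patient on day 77 | 22.9% | 23.75% |
| Every patient on day 78 | 23.2% | 23.9% |
| Evenly spread over days 71-91 | 23.7% | 24.2% |

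For the last row, visits on days 71 to 83 leave 13, 12, …, 1 days uncovered, which sum to 91. Spread over 21 possible days, that is 91/21 = 4.3 days, or 5.2% of the window. Then 25% × (1 − 0.052) = 23.7%, and 25% × (1 − 0.3 × 4.33/42) = 24.2%.

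**5. What the weight rule does to an estimate.** As an illustration, assume one dose with 4 DLTs in 18 and every DLT-free patient last assessed on the same day, with weight w. Maximising p^4 × (1 − wp)^14 gives p = 4/(18w): 22.2% with w = 1, 24.2% with w = 0.917, 26.3% with w = 0.845. This is a single-dose likelihood, not the trial's Bayesian model, whose prior and skeleton are not in the article.

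**6. Other routes to a late DLT.** In calendar weeks, week 18 ± 1 is days 113-133, so the next scheduled assessment is at least 113 − 84 = 29 days after the window closes. On schedule, the last tolinapant dose is day 35, so AE reporting ends at 35 + 30 = day 65, which is 84 − 65 = 19 days before the window closes.

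**The case against.** A reader might infer that a patient seen in trial week 11 is credited in full at that visit. The article does not say so: full weight is tied to completed treatment plus five weeks of follow-up, and a patient seen on day 71 carries 0.845 that day. Nor does it say that follow-up visit 1 closes the window. A reader might also infer that the tolerance contradicts the 12-week period. It does not strictly do so, because follow-up until a DLT or 12 weeks can be met by contact other than that visit. How DLT status is confirmed may be set out in the full protocol or the supplementary file, and its absence here is not the point. What stands is that the visit tolerance and the elapsed-time weight are both fixed in the article and, as written, allow full weight to rest on an earlier check.

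The 13-day gap belongs to one reading only; the reading that reproduces the stated weights gives 7 days. The week-18 assessment could also pick up a DLT from the uncovered days in retrospect. That helps, but decisions taken before that visit would lack it.

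The size is also limited. The worst figures need every patient seen on the first permitted day and nothing learned later. Tolinapant ends at about day 35, and a DLT must be judged definitely or probably related to it, so risk in days 72-84 may well be below uniform. With 18 patients the binomial standard error at 25% is √(0.25 × 0.75/18) = 10 percentage points, far larger than the bias. These points stand, and they are why the matter is minor.

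**Conclusion.** The point holds as a minor one. A compliant follow-up visit 1 can precede the end of the DLT period by up to 7 days (completed weeks) or 13 days (calendar weeks), while the weight continues to 1.0 with no scheduled check of the rest. The under-ascertainment runs one way. Under uniform risk with nothing captured after the visit, a true 25% reads as 21.1% or 22.9% in the two extreme cases, and about 23.7% with visits spread evenly over days 71-91; risk concentrated early makes it smaller.

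It would be tempting to conclude that the trial will select too high an MTD. The documents do not support that: no simulation of the design under this schedule is at hand, and no change in the selected dose has been shown. The case for acting is that the correction is cheap and concerns the primary endpoint.

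**What to change.** Either of two changes is enough:

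- In Table 2, remove the early side of the tolerance so that follow-up visit 1 falls on or after day 84, for example 0 to +7 days, and state whether trial weeks are completed or calendar weeks.
- In the weight rule, give 1.0 only once DLT status to day 84 has been confirmed on or after day 84; until then, calculate the weight to the date of the last DLT assessment. Only events with onset up to day 84 count.

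The first is simpler. The second should be confined to the end of the window: applied throughout, it would hold a patient last assessed at the end of week 7 at 49/84 = 0.583 until follow-up visit 1.

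For either to work, the AE reporting cut-off (about day 65 on schedule) must be reconciled with the 12-week DLT period, so that an event on days 66-84 learned of at the visit is clearly reportable as a possible DLT.

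The cost is one edit to Table 2 or one line in the model specification, plus the reconciliation. No visit is added. Full weight arrives slightly later for some patients, by up to 7 days with the example window, in a design chosen to avoid waiting; partial weights still enter interim decisions in the meantime.
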